#### Secondary outcome measures

After adjustment for the patient’s age, center, and NIHSS score (in an ANCOVA), an independent *t*-test or a Mann-Whitney test will be used to assess intergroup differences in the secondary outcomes: motor skills (including lower limb motricity: the motor part of the Fugl-Meyer Assessment of the lower extremity), gait (10MWT), ambulation capacity (FIM) and balance (TUG)), cognitive skills (neuropsychological assessments of the French validated battery for stroke), personal autonomy (FIM), disability (mRS-SI), and QoL-VAS. As appropriate, Pearson’s correlation coefficient or Spearman's correlation coefficient (r) will be used to assess performance in gait and balance DTs (eight cognitive-motor DTs: phasic, executive, praxis, memory DT 10MWT and DT TUG tasks) and (in a univariate analysis) to identify cognitive and motor determinants correlated with an increment in ST 10MWT speed. We shall rule out multicollinearity by applying standard procedures. Multiple linear regression will then be used to identify factors that are independently correlated with an increment in gait speed.

Between-group comparisons at baseline will be performed using a t-test, a Mann-Whitney test, a Kruskal–Wallis test, a chi-squared test, or Fisher’s exact test, as appropriate. Statistically significant group interactions and factors will be analyzed post hoc. The Bonferroni method will be used to adjust the overall level of significance for multiple testing. All statistical analyses will be performed using SAS software (version 9.3, SAS institute Inc, Cary, NC, USA). The threshold for statistical significance will be set to *p*<0.05. A statistician blinded to the study group assignment will perform the statistical analyses.

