### Eligibility criteria {10}

The inclusion criteria will be as follows: (i) age between 18 and 90, (ii) admission to a rehabilitation department within 6 months of a first ischemic or hemorrhagic stroke with positive brain imaging findings (computed tomography (CT) or magnetic resonance imaging (MRI) of the brain), (iii) ability to provide informed consent, (iv) ability to walk at least 10 m (with or without a technical aid) at a speed below 1.2 m.s^−1^, and (v) social security coverage. The exclusion criteria will be (i) prestroke locomotor or neurological disorders affecting gait, (ii) visual or hearing disorders that impair communication, (iii) severe aphasia, (iv) participation in another interventional study of gait or cognitive rehabilitation, (v) pregnancy or breastfeeding, and (vi) administrative supervision (legal guardianship or incarceration).

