### Outcomes {12}

#### Clinical assessments at baseline (Table 3)

The study population's characteristics recorded at baseline (M0) will include demographic variables (age, sex, and handedness), comorbidities (neuro-orthopedic and bladder disorders), the stroke date, the type of stroke (site, side, and ischemic or hemorrhagic), the stroke severity (National Institutes of Health Stroke Scale (NIHSS) score) [47], neurological impairment (the motor part of the Fugl-Meyer Assessment of the lower extremity [54], the French adaptation of the Harmonization Standards Neuropsychological Battery [50, 55, 56] (Table 4), personal autonomy (the functional independence measure (FIM) [51]), disability (a structured interview with a modified Rankin scale score (mRS-SI) (Table 5) [52]); and QoL on a VAS (QoL-VAS). Qualitative and quantitative gait variables will be assessed with a clinical classification of gait disorders (Supplementary material 1), the single-task 10-m walking test (ST 10MWT) [61], and the FIM's “walking” item [51]. Balance will be assessed in the timed up-and-go (TUG) test. In order to assess CMI, four cognitive-motor DTs will be performed during the DT 10MWT and the DT TUG test: a verbal Trail Making Test (executive function) [59], a symbolic praxis test [60], a literal fluency test [50], and a verbal serial number recall task (short-term memory [62]). The data from the cognitive-motor DTs will be recorded every 15 s, so that participants can be compared regardless of their gait speed [63].

**Table 3 Tab3:** Schedule for the assessment of primary and secondary outcomes

	Recruitment	Inclusion M0	Follow-up visit at M1	Follow-up visit at M2	Follow-up visit at M6

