## Data collection and management

### Plans for assessment and collection of outcomes {18a}

#### The primary outcome measure

The ST 10MWT will be used to compare gait performance in the DT GR and ST GR groups at post-stroke M6. As a single-task assessment of comfortable walking speed during a 10-m walking test, the ST 10MTW is the “gold standard” short-distance test of walking performance in people with stroke [64, 70]. Gait speed is an important determinant of various health aspects, such as vital status, gait ability (balance, mobility limitations, activities of daily living, etc.), and community activities after stroke [11, 61, 67, 71–73].

The ST 10MWT’s psychometric properties are excellent, with strong reliability, construct validity, sensitivity to change across the care continuum after stroke, and excellent clinical test-retest reliability (intraclass correlation coefficients: 0.80–0.99; measurement error: 0.04–0.40) [64]. Gait speed is clinically meaningful and is correlated with measures of strength, balance, and physical activity (*r* = 0.26–0.8, *p* < 0.05) [64]. Each center will receive a training visit and will be given guidelines on performing the ST 10MWT.

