## Statistical methods

### Statistical methods for primary and secondary outcomes {20a}

#### Primary outcome measure

The primary outcome measure will be the ST 10MWT result 5 months after the end of the GR protocol. Depending on the type of data and after adjustment for the patient’s age, center and the NIHSS score in an analysis of covariance (ANCOVA), an independent *t*-test, a Mann-Whitney test, or a generalized linear mixed model will be used to compare the two groups with regard to the 10MWT speed.

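### The determinants analysis screens and regresses the gait-speed increment without securing baseline speed in the model, so a variable that only tracks baseline speed can often be flagged

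*Protocol article*

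**What the plan says.** The determinants analysis is described in the Protocol article under Statistical methods {20a}, Secondary outcome measures. It has three steps.

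1. Pearson or Spearman correlations are used, in a univariate analysis, "to identify cognitive and motor determinants correlated with an increment in ST 10MWT speed".
2. A collinearity step follows: "We shall rule out multicollinearity by applying standard procedures".
3. The final model: "Multiple linear regression will then be used to identify factors that are independently correlated with an increment in gait speed".

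For this analysis the section gives no candidate list, no fixed covariates, no rule for carrying variables forward, and no statement of which visits define the increment.

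Adjustment covariates are named only for the between-group comparisons. For the primary outcome the wording is "after adjustment for the patient’s age, center and the NIHSS score in an analysis of covariance (ANCOVA"; for the secondary outcomes it is "After adjustment for the patient’s age, center, and NIHSS score (in an ANCOVA". Baseline speed is in neither list. It is available, because the M0 assessments include "the single-task 10-m walking test (ST 10MWT".

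Under Plans for assessment and collection of outcomes {18a} the article states: "Gait speed is clinically meaningful and is correlated with measures of strength, balance, and physical activity". It gives r = 0.26 to 0.8 for these correlations, and intraclass correlations of 0.80 to 0.99 for the test itself.

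**The concern.** Two choices are stated in the text and are not left open: the outcome is a change score, and the screen against it is unadjusted. A change score is follow-up minus baseline, so it is arithmetically tied to baseline speed. Unless the slope of follow-up speed on baseline speed happens to be 1, anything that tracks baseline speed correlates with the change, even if it says nothing about follow-up speed once baseline is known.

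Several M0 measures are likely to track walking speed, for example the TUG, the DT 10MWT and the lower-limb Fugl-Meyer score. If baseline speed is not held in the regression, such variables can be reported as determinants of recovery when they are only markers of where the patient started. The collinearity step adds a risk. Baseline ST 10MWT is likely to be collinear with the other timed walking tests, and the unnamed procedure could remove it. The Discussion hopes that gait phenotyping will help target rehabilitation, so misattributed determinants could mislead later work.

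**Working it through.** **The plan's own figure.** The article gives no number for the determinants analysis. Its sample size reproduces closely: n per arm = 2 × (1.96 + 0.842)² × 0.3² / 0.1² ≈ 141.3, so 142 per arm and 284 in total, against the stated 280. For the determinants analysis I take n = 300 × 0.90 = 270 evaluable.

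**Inputs.**
- From the article: two-sided alpha 0.05; SD 0.30 m/s (a chronic-stage figure, used here for M6); candidate correlations with gait speed of 0.26 to 0.8; reliability 0.80 to 0.99.
- Assumed, because the article does not give them: increment = M6 − M0; M0 SD (SD0) of 0.20, 0.25 or 0.30 m/s; M0-M6 correlation r of 0.7, 0.8 or 0.9; a candidate Z correlated 0.5 with M0 speed and unrelated to M6 speed given M0 speed.

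**Formulas.**
- SD(increment) = √(SD6² + SD0² − 2·r·SD6·SD0)
- corr(M0, increment) = (r·SD6 − SD0) / SD(increment)
- corr(Z, increment) = 0.5 × corr(M0, increment)
- Chance of p<0.05 by Fisher z: Φ(m − 1.96) + Φ(−m − 1.96), with m = atanh|corr| × √267

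**One case in full.** SD0 = SD6 = 0.30, r = 0.7. SD(increment) = √0.054 = 0.232. corr(M0, increment) = (0.21 − 0.30)/0.232 = −0.387. corr(Z, increment) = −0.194. m = 0.196 × 16.34 = 3.20, so the chance is Φ(1.24) ≈ 89%.

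**All nine cases.**

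| SD0 | r | slope of M6 on M0 | corr(Z, increment) | flagged |
|---|---|---|---|---|
| 0.20 | 0.7 | 1.05 | +0.02 | 7% |
| 0.20 | 0.8 | 1.20 | +0.11 | 43% |
| 0.20 | 0.9 | 1.35 | +0.24 | 98% (97.6%) |
| 0.25 | 0.7 | 0.84 | −0.09 | 32% |
| 0.25 | 0.8 | 0.96 | −0.03 | 7% |
| 0.25 | 0.9 | 1.08 | +0.08 | 24% |
| 0.30 | 0.7 | 0.70 | −0.19 | 89% |
| 0.30 | 0.8 | 0.80 | −0.16 | 74% |
| 0.30 | 0.9 | 0.90 | −0.11 | 45% |

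Across the article's range for the candidate correlation (0.26, 0.5, 0.8), with equal SDs, the rates are 38%, 89% and 99.9% at r = 0.7, and 16%, 45% and 84% at r = 0.9.

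**What holding baseline in the model does.** Simulation, 3,000 runs per scenario, n = 270, candidate correlation 0.5. With SD0 = 0.30, an error-free baseline and r = 0.5, 0.7 or 0.8, the flagging rate is 99%, 90% or 74% without M0 speed and about 5% in each case with it. If M0 speed is merely one of the candidates and is kept, it passes the screen in every run and the whole two-step procedure flags Z in 3% to 4% of runs.

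**With measurement error in M0 speed.** SD0 = 0.30, r = 0.8 between observed speeds, Z correlated 0.5 with true M0 speed. At reliability 0.90, Z is flagged 25% of the time with observed M0 speed in the model and 28% without. At 0.80 the rates are 79% with and 5% without; with r = 0.7 and reliability 0.80 the rate with M0 speed is 52%. At reliability of 0.97 or more, entering M0 speed keeps the rate at about 5% to 10%.

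**The case against.** A reader might infer that the plan leaves baseline speed and arm out of the regression, and so that spurious determinants will be reported, typically with the wrong sign. The document does not support that reading.

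- **Silence is not exclusion.** The article lists no covariates for this regression, and a condensed article may leave the list to the full protocol or analysis plan. M0 ST 10MWT speed is a motor variable and could enter as a candidate. If kept, it largely removes the problem when baseline is measured without error. Arm may also be modelled, since the section mentions group interactions.
- **The rates above are for the screen.** They carry over to the final model only if M0 speed is omitted or dropped. They also use an uncorrected 0.05; the section mentions Bonferroni adjustment without saying whether it covers this analysis.
- **Size and direction are assumption-bound.** Equal SDs at M0 and M6 are doubtful: the article quotes a subacute mean of 0.34 m/s and a chronic mean of 0.84 m/s, and entry requires "ability to walk at least 10 m (with or without a technical aid) at a speed below 1.2 m.s^−1". With a slope near 1 the inflation almost vanishes, and above 1 the sign reverses.
- **The quoted correlations are not for cognition.** The range 0.26 to 0.8 concerns strength, balance and physical activity.
- **Adjustment is not free.** At the low end of the article's own reliability range, entering observed baseline speed can do worse than leaving it out.

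All of this stands, and it limits the claim to what can happen. It does not rescue the two steps that are written down: selecting on unadjusted correlations with a change score, and an unnamed collinearity step that could remove the variable that offers protection.

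**Conclusion.** The point holds in limited form. The plan fixes an unadjusted screen against the gait-speed increment, then regresses that increment without securing M0 speed in the model. A candidate that only tracks baseline speed can often be flagged: about 7% to 98% of the time against a nominal 5%, for a candidate correlated 0.5 with an error-free baseline at n = 270. That range rests on an assumed SD0 of 0.20 to 0.30 m/s, SD6 of 0.30 m/s, an M0-M6 correlation of 0.7 to 0.9, and an increment taken as M6 minus M0. The spurious association is negative when the slope of M6 on M0 is below 1 and positive when it is above.

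This is a secondary, exploratory analysis, and neither the primary comparison nor any other between-arm comparison is affected. The wording should be changed, but the trial's main conclusion does not depend on it.

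**What to change.** Amend the description of the determinants analysis as follows.

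1. State which visits define the outcome.
2. Model M6 ST 10MWT speed, with M0 ST 10MWT speed and arm as fixed covariates in every model, including single-predictor ones. Keeping the increment as outcome gives the same coefficients for the other predictors, provided M0 speed is always in the model.
3. Exempt M0 speed and arm from the collinearity removal step.
4. Replace the unadjusted screen with a pre-listed set of predictors.
5. Add a sensitivity analysis, either a measurement-error correction or the change-score model alongside, and describe the results as exploratory.

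The cost is wording and one extra analysis; M0 speed is already scheduled for every participant. The real downside is that adjusting for a baseline measured with error can leave or create false associations toward the low end of the reported reliability range. The fifth item is therefore part of the fix.

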### *Sample size {14}*

According to Severinsen et al., the mean ± standard deviation 10MWT speed among stroke victims at the chronic stage is 0.84 ± 0.3 m.s^−1^ [65]. With an alpha coefficient of 0.05 (in two-tailed tests), a power of 80%, and a gait speed standard deviation of 0.3 m.s^−1^, we have calculated that a sample size of 280 patients (140 per group) will be needed to evidence a gait speed increment of 0.1 m.s^−1^ (a magnitude known to be clinically relevant after stroke [66–69]).

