## Assignment of interventions: allocation

### Sequence generation {16a}

The randomization procedure will be prepared by a data manager in the Clinical Research and Innovation Directorate (*Direction de la Recherche Clinique et de l'Innovation*, DRCI) at Amiens Picardie University Medical Center and implemented using Ennov Clinical® electronic data capture software (version 8.0.140, Ennov, Paris, France). The participants will be randomized (1:1) after inclusion and the baseline screening assessments at M0. To obtain groups that are balanced with regard to the stroke prognosis, stroke severity, and center, participants will be stratified by age (<45, 45 to 64, and ≥65), severity (according to the NIHSS score: < 5, 6 to 24, and ≥25), and center (1 to 12).

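### For its multiplicity-adjusted tests the protocol names plain Bonferroni; Holm's step-down version gives the same familywise error control with somewhat more power, at the cost of one word (minor improvement)

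*Protocol article*

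**What the plan says.** All references are to the protocol article.

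- **Statistical methods {20a}, Secondary outcome measures.** The groups are compared on lower-limb motor function, gait, ambulation, balance, the cognitive battery, autonomy, disability and quality of life. The eight dual tasks are assigned to correlation coefficients. The closing paragraph says "Statistically significant group interactions and factors will be analyzed post hoc", then "The Bonferroni method will be used to adjust the overall level of significance for multiple testing". After a sentence on software it adds "The threshold for statistical significance will be set to" p<0.05. It does not list the tests that share the correction or say how many there are.
- **Plans for assessment and collection of outcomes {18a}.** Secondary outcomes are measured at M1, M2 and M6.
- **Statistical methods {20a}, Primary outcome measure.** There is one primary outcome, the single-task 10-m walking test 5 months after the end of the programme. No multiplicity adjustment is mentioned for it.
- **Sample size {14}.** The calculation starts "With an alpha coefficient of 0.05 (in two-tailed tests), a power of 80" percent, takes "a gait speed standard deviation of 0.3 m.s^−1", aims "to evidence a gait speed increment of 0.1 m.s^−1", and concludes that "a sample size of 280 patients (140 per group) will be needed". The 0.05 is not divided.

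**The concern.** The secondary measures overlap heavily: several walking and balance tests, two uses of the functional independence measure, and a long battery of related cognitive scores, most of them at three visits. Plain Bonferroni holds every one of these tests to the overall level divided by the total number, however many of the others have already been rejected. Holm's step-down procedure relaxes the divisor after each rejection and gives the same guarantee. By naming the single-step version, the plan gives up some chance of detecting real secondary effects and gains no error control in return.

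A smaller point of clarity goes with it. The 10-m walking test is also listed as a secondary outcome, and secondary outcomes are measured at M6, the visit of the primary outcome. No sentence says outright that the M6 gait-speed test stands outside the correction.

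**Working it through.** **1. The plan's own figure.** Inputs from Sample size {14}: difference 0.1 m/s, SD 0.3 m/s, two-sided alpha 0.05, power 80%. Allocation is 1:1 (Sequence generation {16a}).

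n per group = 2 × (1.960 + 0.842)² × (0.3/0.1)² ≈ 141.3, so 142 per group or 284 in total, against the stated 280. At 140 per group the expected test statistic is 0.1 / (0.3 × √(2/140)) = 2.789, and power is Φ(2.789 − 1.960) = 79.6%. The planned size therefore rests on a primary test at undivided 0.05.

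**2. How many tests (assumption).** The protocol gives no number. Counting from the {20a} list and Table 4:

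| Content | Measures | Tests over 3 visits, less the primary |
|---|---|---|
| 7 non-cognitive (Fugl-Meyer, 10MWT, FIM walking, FIM, TUG, mRS-SI, QoL) + 13 cognitive scores, one per line of Table 4 | 20 | 20 × 3 − 1 = 59 |
| The same 7 + 16 cognitive scores, multi-part lines split | 23 | 23 × 3 − 1 = 68 |
| As the row above + 8 dual tasks | 31 | 31 × 3 − 1 = 92 |
| As the row above + NIHSS | 32 | 32 × 3 − 1 = 95 |

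The last two rows treat the dual tasks as between-group tests, which the text does not say. I use 23 as the size of a one-visit family.

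**3. Why Holm cannot do worse.** Order the p-values from smallest to largest. Holm compares the i-th with 0.05/(m − i + 1) and stops at the first failure. Every threshold is at least 0.05/m, so whatever Bonferroni rejects, Holm rejects too. For error control, let m₀ be the number of true null hypotheses. The first false rejection can occur no later than step m − m₀ + 1, so it needs a true-null p-value of at most 0.05/m₀. By the Bonferroni inequality that has probability at most 0.05, whatever the dependence.

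**4. Size of the gain.** Assumed: 140 per group, standardised effect 1/3 for every real effect (the ratio 0.1/0.3 used for the primary outcome), and equal correlation 0.5 between test statistics. Bonferroni power per test is Φ(2.789 − z), where z is the two-sided critical value at 0.05/m:

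- m = 23: 0.05/23 = 0.00217, z = 3.065, power 39%.
- m = 92: 0.05/92 = 0.00054, z = 3.458, power 25%.

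Simulated average power over the real effects (20,000 runs):

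| m | Half real: Bonferroni → Holm | All real: Bonferroni → Holm |
|---|---|---|
| 23 | 39.0% → 41.7% | 38.9% → 48.7% |
| 31 | 35.8% → 38.4% | 35.9% → 45.1% |
| 59 | 29.3% → 31.4% | 29.3% → 36.6% |
| 68 | 28.0% → 30.0% | 28.0% → 34.9% |
| 92 | 25.4% → 27.2% | 25.4% → 31.6% |

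At 95 tests the gains are 1.8 and 6.1 points. With half the effects real, Holm's simulated familywise error was between 2.3% and 2.8%, below the 5% limit.

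**The case against.** **Bonferroni is a legitimate prespecified choice.** This stands. It controls familywise error under any dependence and gives simple simultaneous confidence intervals. The gain from Holm is modest, and the larger figures require every secondary effect to be real. The low power per test comes mainly from the number of tests, which Holm does not change.

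**The scope of the Bonferroni sentence is uncertain.** It directly follows the sentence on post hoc analysis of interactions and factors and may cover only those. That also stands. The gain would then differ, but Holm would still reject at least as much in whatever family is meant. Listing the family is commonly left to an analysis plan, which is not shown here, so its absence is not held against the article.

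**Stronger readings that a reader might infer.**

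- *Two conflicting thresholds.* The two sentences fit together if 0.05 is the overall level that Bonferroni divides or, equivalently, if adjusted p-values are compared with 0.05.
- *A near-certain chance finding.* An unadjusted 0.05 over 92 independent tests would give 1 − 0.95^92 = 99%. That ignores the stated correction, and at correlation 0.5 the simulated figure is about 76%.
- *A primary test that loses most of its power.* With the primary in a family of 93, alpha would be 0.05/93 = 0.00054 and power about 25%. The subheading, the single unadjusted primary outcome and the sizing at undivided 0.05 all point against that reading.

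**Conclusion.** A minor point: a cheap improvement to a valid method, not the correction of an error. That Holm is at least as powerful with the same familywise guarantee is a mathematical fact and needs no assumption about the number of tests or their correlation. The size of the gain does rest on assumptions: 23 to 95 tests, correlation 0.5, a standardised effect of 1/3 and 140 per group. On those it is about 2 to 3 points of average power when half the effects are real and about 6 to 10 points when all are, with the larger gains in the smaller families. The documents do not support a claim that the thresholds contradict each other or that the primary test is underpowered by the correction. Saying that the primary test is outside the family only makes explicit what the sample size already implies.

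**What to change.** In {20a}, replace Bonferroni with Holm (Bonferroni step-down) for the multiplicity-adjusted tests, and say that Holm-adjusted p-values are compared with 0.05. In the same sentence, confirm that the M6 single-task 10-m walking test is tested alone at two-sided 0.05 and does not belong to that family.

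The cost is a one-word change plus a clarifying clause, and a standard option in the SAS software already named. It needs no extra patients, visits or data. The one real drawback is that simultaneous confidence intervals matching Holm are less simple than Bonferroni intervals.
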